## 7 DESCRIPTION OF STUDY PROCEDURES

### 7.1 Assessments

Study assessments will be performed at the times outlined in the [Time & Events Table](#).

#### 7.1.2 *Medical History*

When consent/permission, and assent have been obtained and the HIPAA document signed, a focused medical history concerning the treatment protocol and treatment exposures to date will be performed through extraction of a limited set of data from the adolescents' electronic medical record.*Equiti Foods Registration*

At enrollments, parents will be assisted with establishing an account at enrollment, and then helping the parent sign-in to confirm that the account exists.

### 7.2 Study Surveys and Interviews

Blank copies of the study measures are in [APPENDIX II – Study Measures](#), and the semi-structured interview guides are in APPENDIX III – Study Semi-Structured Interview Guides. The study survey will include socio-economic items and established measures. Study variables, sources, measures, data collection time-points are shown in Time & Events Table. The measures were selected to assess each of the pathways shown in Figure 1 and domains of feasibility. Except for the acceptability, feasibility, affordability and accessibility items, the study measures have been used in multiple prior studies of pediatric oncology populations and performed well.

#### 7.2.1 *Surveys and Interview Questions for Adolescents*

Adolescents will be asked to complete (a) a brief investigator-developed socio-demographic survey at baseline (T1), (b) established measures of alterations in taste and chemotherapy induced alterations in taste at weeks 4, 8, and 12 (T2-4) at the start of their semi-structured interviews, and (c) a person-reported measure of acceptability and appropriateness at week 12 (T4).

Socio-demographic items will ask the adolescent to tell us their current age (in years), sex at birth, race, the language they mainly use at home, and their current grade (year) in school.

---

Chemotherapy-induced alterations in taste will be measured by 13-items from the Chemotherapy-Induced Alterations in Taste Scale (CiTAS) [50]. Adolescents will be asked to use a 5-point scale to indicate how much the taste change bothered them this week. Scores will be calculated by summing item responses and dividing by 13 (lower scores indicate less alteration in taste).

Other chemotherapy-related symptoms will be measured by the 15-item Symptom Screening in Pediatrics (SSPedi) tool. [51] Adolescents will be asked to use a 5-point scale anchored by 0 (not at all) and 4 (worst bother) to indicate how much each symptom bothered them today or yesterday. Scores will be calculated by summing item responses. Scores can range from 0-60; lower scores indicate less symptom severity.

Semi-structured interviews will focus on the adolescent's experience with a study provided meal and their recommendations for improvements.

Adolescent-reported acceptability and appropriateness of the MTM-Kids program will be assessed using items that tap into each of these domain. The original items were developed and validated by Weiner and colleagues for use in studies that examine adopters' perspectives on the acceptability, etc. of implementing entire evidence-based programs in practice.[52] For this feasibility study, the Weiner, et al. items served as the basis for assessing areas that may affect participants' perspectives on specific aspects of the MTM program. Each domain has 4-items. Adolescents will be asked to read each item and indicate their response using 5-point scales anchored by 1=completely disagree and 5=completely agree. Domain scores will be calculated by summing item responses and dividing the sum by 4. Domain score range is 1-4, with higher scores indicating better acceptability or appropriateness.

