Food is Medicine interventions (conjunctions of food and healthcare that aim to increase access to nutritious food and thus support health)[44] include offering: (a) prescriptions for produce (vouchers for food items that may require preparation), (b) medically tailored groceries (food items that may require preparation), and (c) MTMs (home-delivered, ready to heat-and-eat meals designed by a registered dietician).[44] MTMs are the most intensive type of Food is Medicine intervention, indicated for persons with substantial physical and/or contextual barriers to preparing healthy meals. Contextual barriers apply to households in which parents navigate the caregiving demands of serious pediatric illness. Short term MTMs (high risk pregnancy), or long-term MTMs (AIDS, diabetes, organ failure) improve outcomes and reduce health care costs for adult populations with SDOH inequities. [25, 44] To our knowledge, MTM interventions have not been tested in pediatric serious illness populations for which nutrition is a known, important predictor of treatment success, long-term health, and well-being. Historically, needs of pediatric populations have received little attention – children lack political clout and thus disparities for pediatric populations persist.[45] This study is a first step towards system-level interventions that embed equity into holistic care delivery for pediatric populations with serious illness. Areas of uncertainty to be addressed by this feasibility study prior to deciding whether to proceed with a future definitive trial [46] include the (a) feasibility of recruiting and retaining a sample; (b) feasibility of MTM ordering and delivery, and acceptability, affordability, accessibility, and appropriateness of MTM for the target population, and (c) sensitivity of proposed pathways to MTM.

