### 4.1 Study Intervention

We will enroll 5 adolescent + 5 parents (5 dyads) in the formative test, and then 10 adolescents + 10 parents (10 dyads) in the validation test for a total of 15 adolescents and 15 parents. The sample size is based on evidence that testing with 5 users identifies 85% of barriers and facilitators to accessing program materials and putting them to use to inform refinements, and 3 iterations of feedback per user during the testing period identifies 98% [47, 48] Thus, we expect that 15 dyads total with 3 iterations of feedback via semi-structured interviews with the adolescent and also with the parent over the 12-week study period will provide sufficient data to uncover aspects of study processes and the program materials that need refinement prior to efficacy testing. For the formative and evaluative tests, we will use unique sets of dyads to gain a broader perspective than is possible with the same sets. We will also focus on children in the adolescent age group (ages 12-17.9 years) for this more in-depth data collection because they are more likely than younger children to express opinions independent of parental influence.[49]

Equiti Foods will tailor flavorings and deliver selected meals along with condiments to enable individualization by household members. The intervention will be 12-weeks duration, with weekly "doses" (meal deliveries) of up to 10 meals per week, as suggested by MTM studies with adult populations. [32, 44] Twelve weeks duration enables three iterations of feedback about the prior month's experience with MTM-Kids.

Participation will require (a) completing a survey at baseline (T1), receipt of MTM-Kids over 12 weeks, (b) participating in interviews at 4, 8, and 12 weeks (T2, T3, T4) after starting to receive meals to inform refinement, and (c) completing a follow-up survey at 12 weeks (T4). While we will not ask participants to forgo other forms of food-related assistance, we will ask them to tell us about food assistance requested and received. Interested dyads will join the informed consent/assent process, complete baseline surveys, and set up an account on Equiti Food's website where they can select/order the first MTM allotment.

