Adolescents and parents will also be asked to participate in three audio-recorded individual semi-structured interviews via an IRB-approved secure platform or in person during the next regularly scheduled clinical visit based on their preference. Interviews will last 20-30 minutes. Parents will help adolescents enter video sessions (we expect most adolescents will be familiar with this process from online schooling during the pandemic). A team member with training in clinical care and research of adolescents and families will conduct the interviews. First, adolescents will be asked to complete validated measures of symptoms [50] and chemotherapy induced alterations in taste [51], say which meal they tried (or considered trying), then answer questions about how that worked for them (or didn't) and recommendations for improvements (nutritional pathway). Parent interviews will focus on logistics (meal selection, ordering, delivery, timing), meal use relative to treatment-related events and associated caregiving demands (time-demands pathway), and allotment adequacy (cost-coping pathway).

---

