### Footnotes to Time & Events Table

1. Screening includes tests to confirm eligibility.
2. Informed consent will include (a) adult consent from the parent for their participation in the study, (b) parental permission for their adolescent's participation, and (c) adolescent assent. HIPAA authorization to extract a

limited set of data from the adolescent's electronic medical record. Completion of the parent contact form, baseline assessments and Equiti Food account set-up will commence after the written consent/permission/assent have been obtained.

3. Parent participants must register with the Equiti Foods Website in order to select and order MTM allotment. Allotment will be weekly (up to 10 meals per week), for 12 weeks. Delivery will take 3-5 days and parents can order up to 5 working days in advance.
  4. Adolescents will complete surveys at baseline, T2, T3 and T4. See [ADOLESCENT SURVEYS](#)
  5. Parents will complete surveys at baseline and at 12 weeks (T4). See [PARENTAL SURVEYS](#)
  6. A limited set of data (specified in the HIPAA authorization form) about the adolescent's cancer diagnosis, diagnosis date, treatment protocol, treatment initiation date, and treatment exposures to date will be extracted from the adolescent's electronic medical record.
  7. Gift cards will be given following completion of the Baseline and then the 12-week survey, and following completion of the Week 4, 8 and 12 interviews. The gift cards value will be \$15 for parent and \$15 for the child, for a possible total of \$75 for parent and \$75 for child.
  8. Parents will be contacted within 1 week following baseline data collection to verify that they have placed the initial meal order, and problem-solve as indicated.
  9. Semi-structured interviews will be conducted and audio-recorded via an IRB-approved secure video platform, or in-person during a regularly scheduled clinical visit according to the participant's preference. An investigator-developed interview guide will inform the interviews (see [APPENDIX III – Study Semi-Structured Interview Guides](#)).
-

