## **8.3      Data Analysis Plans**

### **8.3.1      *Primary Endpoint Analysis***

For project to be considered successful and feasible in a larger study, we determined the following benchmarks: a) 70% of those approached are enrolled in the study, (b) 10 out of 15 participating parent/adolescent dyads should complete the baseline and week 12 surveys, (c) 10 out of 15 parents receive at least 4 weeks of meal deliveries, and (d) in 10 out of 15 dyads, the adolescent and the parent each complete at least one interview (week 4, 8, or 12). We will estimate the retention rate and report it with a 95% confidence interval.

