### **8.3.3      *Exploratory Endpoint Analysis***

Descriptive statistics (mean total scores, score ranges, standard deviations) and figures will be used to portray the results of baseline (T1) and 12 weeks (T4) assessments of household food insecurity, household nutrition insecurity, parental financial coping strategies, parental time demands, and parental financial wellbeing.

Descriptive statistics (mean total score, score range, SD) will be used to portray adolescents' treatment-related symptoms and chemotherapy-induced alterations in taste.

Qualitative descriptive approaches will be used to identify themes in the interviews with adolescents and parents about their experiences with MTM-Kids meals and recommendations for needed improvements.

---

Treatment exposures, scores on assessments of symptom and chemotherapy induced alterations in taste will be used to qualitatively explore linkages between symptoms, alterations in taste, and themes in the interview data.

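### No taste or symptom score is scheduled before the meals start, and later scores depend on an interview taking place

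*Protocol*

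**What the plan says.** Section 7.2.1 gives adolescents "a brief investigator-developed socio-demographic survey at baseline (T1") and places the taste measures "at weeks 4, 8, and 12 (T2-4) at the start of their semi-structured interviews". That sentence names taste twice and omits symptoms, so the symptom timing rests on two other places. Section 4.1 says of the interviews: "First, adolescents will be asked to complete validated measures of symptoms", followed by the taste measure. Table 1 marks symptoms and taste at T2 to T4. (In the copy read here the adolescent rows of Table 1 sit one line out of step; read with that shift, they agree with the text.) Section 4.1 sets time zero: "participating in interviews at 4, 8, and 12 weeks (T2, T3, T4) after starting to receive meals".

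Footnote 4 to Table 1 says "Adolescents will complete surveys at baseline, T2, T3 and T4" but does not say which instruments are used at which visit.

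On use, Section 1.2 lists "sensitivity of proposed pathways to MTM" among the uncertainties the study is to address, and Section 7.2 says the measures were chosen to cover each pathway. Section 8.3.3 plans descriptive summaries of the two scales and adds that "scores on assessments of symptom and chemotherapy induced alterations in taste will be used to qualitatively explore linkages" with interview themes. Section 8 plans to explore biological sex in the taste and meal-acceptability data. Benchmark (d) in 8.3.1 asks that in 10 of 15 dyads "the adolescent and the parent each complete at least one interview".

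**The concern.** The parent and household measures have a T1 and a T4 value. The adolescent pathway, taste and symptoms, has no value before exposure to the meals. Adolescents may enter at any point after one completed cycle with at least two more expected, so their taste and symptom state at entry is likely to vary. Without a T1 score, a contrast seen at week 4 or later, for example by sex or by how well the meals were received, may have been present before the first delivery.

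The second part concerns retention, which is the primary objective. Symptom burden is a plausible reason for leaving or for not ordering. Because both forms are given only inside the interview, an adolescent who leaves before week 4 has no scheduled score, and those who leave cannot be compared with those who stay on these scales.

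**Working it through.** The protocol states no figure that depends on this schedule, so there is nothing to reproduce. The check sets the schedule against the planned uses and counts the scores that can exist.

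**Inputs.** 15 dyads (8.1). Interviews at weeks 4, 8 and 12 from the start of meals (4.1). Benchmark (d): 10 of 15 dyads, at least one interview by each member (8.3.1). Recall periods: the current week for taste, today or yesterday for symptoms (7.2.1).

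**Is there any pre-meal score?**
- Adolescent T1 survey: socio-demographics only.
- T1 medical record form (15.2.1.1): diagnosis, treatment, height and weight; no taste or symptom item.
- Eligibility screener (15.2.2.8): one yes/no item, answered by the parent, on whether food has tasted different since chemotherapy began. This is not a scale score and does not cover symptoms.
- Result: 15 × 0 = 0 pre-meal scores on either scale.

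**Can it be recovered later?** No. With recall of one week and about two days, a week-4 form cannot reconstruct the state before the meals, and a later form cannot replace a missed one.

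**How many scores can exist during the meals?**
- Maximum per scale: 15 × 3 = 45.
- Fewest compatible with benchmark (d): 10 × 1 = 10, and 10/45 = 22%.
- Most adolescents with no score while (d) is met: 15 − 10 = 5, and 5/15 = 33%.

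The last figure is a bound. Benchmark (d) is judged per dyad, so a dyad can fail it because the parent missed every interview while the adolescent has scores.

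**Illustration.** The protocol gives no interview completion rate, so the rates below are assumptions. An adolescent lacks every score only if all three interviews are missed. With completion probability p per interview:
- Independent interviews, probability (1 − p)³: at p = 0.70, 0.3³ = 0.027, or 0.027 × 15 = 0.4 adolescents; at p = 0.50, 0.5³ = 0.125, or 0.125 × 15 = 1.9.
- The other extreme, where an adolescent attends all three or none, probability 1 − p: at p = 0.70, 0.3 × 15 = 4.5; at p = 0.50, 0.5 × 15 = 7.5, which would fail benchmark (d).

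The number with no score therefore depends mainly on whether missed interviews cluster in the same adolescents.

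**The case against.** The strongest reply is that nothing in the plan needs a baseline taste score. Taste and symptoms are absent from objective 2.3.1, from the T1-to-T4 endpoint in 3.3.1 and from the signals of change that Section 8 uses for the future sample size. Section 8.3.3 links the scores to interview themes, which calls for a score taken at the interview. The protocol attributes taste change to the illness and its treatment and tailors the meals to it; it never says the meals should lower these scores. A single T1 value during ongoing chemotherapy would also be a limited baseline. All of this stands, and it limits the weight of the point.

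Three stronger readings are tempting, and the document does not support them:
- A reader might infer that anyone who stops early or skips an interview has no score. Missing one or two interviews loses those time points only, and stopping after week 4 leaves earlier scores in place. Section 6.1 asks those who stop the intervention whether they may still be contacted for scheduled assessments, 6.4 provides for rescheduling, and 6.3 seeks a final evaluation at withdrawal, though it names no instruments.
- A reader might infer that taste or symptoms as a reason for not eating, not ordering or leaving would be invisible. The adolescent guide (15.3.2) asks why no meal was tried and how it tasted and smelled; the parent guide (15.3.1) asks why orders were less than weekly; 6.1 records reasons for stopping and 6.3 seeks reasons for withdrawal.
- A reader might put the gap at 4 of 12 weeks (33%). With recall this short, no schedule of three forms covers the weeks between them, so that percentage means little.

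None of these replies supplies a pre-meal score.

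**Conclusion.** The point holds as a low-cost design improvement, not as a contradiction or an endpoint that fails. No adolescent (0 of 15) has a taste or symptom score before the meals, although Section 1.2 raises the sensitivity of the pathways as a question and Section 7.2 says each pathway is measured. Entry differences on these scales cannot be separated from differences during the meals, and adolescents who leave before any interview cannot be described on them. The bound of 5 of 15 rests on benchmark (d) being met exactly and on the adolescent, not the parent, being the one who missed in all five dyads. The reading of Table 1 assumes the one-row shift; Sections 4.1 and 7.2.1 support the same schedule without it.

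**What to change.** 1. In 7.2.1 and Table 1, add the taste and symptom forms to the adolescent T1 survey, which Section 4.1 already places before the first order, and have footnote 4 name the instruments at each visit.
2. Keep both forms at the start of the week 4, 8 and 12 interviews, where the thematic linkage needs them, but offer them at those weeks even when the interview does not take place.
3. In 8.3.3, report T1 taste and symptom scores descriptively, overall and by retained or not retained.

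The cost is 13 + 14 = 27 extra items at baseline for adolescents on chemotherapy (28 if the symptom tool has the 15 items stated in 7.2.1, not the 14 in Table 1 and the appendix; that count needs reconciling anyway). Both forms already exist, and the adolescent already completes a T1 survey. A form returned without an interview has no themes from that visit to link to, so its use is descriptive. With 15 adolescents, the retained/not-retained comparison might set 10 against 5 or fewer, so it should carry no test. The change has to be in place before an adolescent's first delivery, because the value cannot be obtained afterwards.

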### **7.2.2 Surveys and Interview Questions for Parents**

Parents will be asked to complete established measures of household food and nutrition insecurity, time-demands, financial cost-coping behavior and financial wellbeing,

Household food insecurity will be measured by the 6-item Food Security Scale [53]. Parents will be asked to indicate whether they experienced the condition during the past 3 month and, in some cases, how often. Scores will be estimated by counting the number of affirmative responses (yes, sometimes, or often); these scores can be categorized, such that 0-1=very low food insecurity, 2-4= low food insecurity, and 5-6=high food insecurity. [53]

Household nutrition insecurity will be measured by the 4-item Nutrition Security Scale plus 2 items from the Healthfulness Choice Scale. [54] Parents will be asked to use a 5-point scale, anchored by 1=never and 5=always, plus a don't know/prefer not to answer option. Scores will be estimated by counting the number of affirmative responses (sometimes, often, or always); these scores can be categorized such that 0-

---

1=very low nutrition insecurity, 2-4= low nutrition insecurity, and 5-6=high nutrition insecurity. [54]

Parental role time-demands will be measured with a set of Patient-Reported Outcome Measurement System v.2 (PROMIS v.2) items that ask about satisfaction with perceived social role performance. [55] Parents will be asked to respond to the PROMIS items using a 5-point scale anchored by 1=not at all and 5=very much. Item responses will be summed and scored using the T-score metric. Higher scores indicate greater satisfaction with social role performance. [55]

Financial coping behaviors will be measured by 7 of the questions from the Financial Coping Behaviors Scale currently being asked in a study of financial distress during treatment of pediatric acute lymphoblastic leukemia (ALL; ACCL20N1CD). [56] Parents participating in MTM-Kids will only be asked about financial coping strategies with implications for the health of the adolescent or another family member. Parents will be asked to use a 3-point response scale anchored by 0=never and 2=several times) to indicate how often they used each coping behavior in the prior month. Item responses will be summed for a total score that can range from 0-14.[56]

Financial wellbeing will be measured by the 8-item Personal Financial Well-being Scale (PFWS). [57] The PFWS uses a 10-point response scale. Scores are calculated by summing item responses and dividing by 8. Scores can range from 1 to 10, with 1 indicating poorest financial wellbeing and 10 indicating highest financial wellbeing. The PFWS has undergone rigorous psychometric testing to establish validity of the latent construct, psychometric properties and norms. [57]

Parent-reported acceptability, appropriateness, feasibility, affordability, and accessibility of the MTM-Kids program will be measured using of the MTM-Kids program will be measured using items developed by others for use in studies examining concerned with the implementation of evidence-based interventions in practice [52] and adapted for this feasibility study. Each domain has 4-items. Parents will be asked to read each item and indicate their response using 5-point scales anchored by 1=completely disagree and 5=completely agree. Domain scores will be calculated by summing item responses and dividing the sum by 4. Domain score range is 1-4, with higher scores indicating better MTM program acceptability, appropriateness, feasibility, affordability, or accessibility. [52]

---

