## 15.2.2 PARENTAL SURVEYS

### 15.2.2.1 Food Insecurity

These statements are what people have said about their food situations. Please tell us whether the statement was often true, sometimes true, or never true for you in the last 6 months.

1. "The food that I bought just didn't last, and I didn't have money to get more."
    - a. Often true
    - b. Sometimes true
    - c. Never true
    - d. Don't know or prefer not to answer
  2. "We couldn't afford to eat balanced meals."
    - a. Often true
    - b. Sometimes true
    - c. Never true
-

- d. Don't know or prefer not to answer
- 3. In the last 3 months, did you or other adults in your household ever cut the size of your meals or skip meals because there wasn't enough money for food?
  - a. Yes
  - b. No (Skip AD1a)
  - c. Don't know or prefer not to answer (Skip AD1a)

[If YES above, then]

- 4. How often did this happen – almost every month, some months, but not every month, or in only 1 or 2 months?
  - a. Almost every month
  - b. Some months but not every month
  - c. Only 1 or 2 months
  - d. Don't know or prefer not to answer
- 5. In the last 3 months, did you ever eat less than you felt you should because there wasn't enough money for food?
  - a. Yes
  - b. No
  - c. Don't know or prefer not to answer
- 6. In the last 3 months, were you ever hungry but didn't eat because there wasn't enough money for food?
  - a. Yes
  - b. No
  - c. Don't know or prefer not to answer

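### Food-insecurity item 4 cannot be scored as written: none of its answers is in the counting rule, and two of them mean the same thing in a 3-month window

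*Protocol*

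**What the plan says.** Section 7.2.2 names the instrument: "Household food insecurity will be measured by the 6-item Food Security Scale". It gives the recall period and response type: "Parents will be asked to indicate whether they experienced the condition during the past 3 month and, in some cases, how often". The counting rule is "Scores will be estimated by counting the number of affirmative responses (yes, sometimes, or often", and the bands are "0-1=very low food insecurity, 2-4= low food insecurity, and 5-6=high food insecurity".

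The form is in section 15.2.2.1. Item 3 carries its own window: "In the last 3 months, did you or other adults in your household ever cut the size of your meals or skip meals" for lack of money. A parent who answers *yes* goes on to item 4: "How often did this happen – almost every month, some months, but not every month, or in only 1 or 2 months". The answers to item 4 are those three frequencies plus a don't-know or decline option. A parent who answers *no* or declines at item 3 skips item 4.

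Section 8.3.3 reports means, ranges and SDs of the score at T1 and T4. Section 8 intends SDs and CIs for change in food-related insecurities, among other domains, to help size the efficacy trial.

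**The concern.** The counting rule and the form do not fit together at item 4, in two ways.

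First, the rule lists the answers that earn a point, and item 4 offers none of them. The form has six items and the bands run to 6, so item 4 is evidently meant to count, but 7.2.2 does not say which of its answers do.

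Second, two of the three frequency answers describe the same households once the window is 3 months. A parent whose household cut meals in 1 or 2 of the last 3 months can truthfully tick either. An analysis plan can later pool the two answers. It cannot tell 1 month from 2 months once the form has been used.

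At stake are the value of a reported score, the band a household falls in, and the SD carried into planning the next trial.

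**Working it through.** **Inputs.** Six items, the counted answers *yes*, *sometimes* and *often*, and bands 0-1, 2-4 and 5-6 (section 7.2.2). Response options, the skip after item 3 and item 3's 3-month window (section 15.2.2.1). Fifteen parents (section 8.2.2).

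**Step 1: the plan's own maximum.** Six items and a 5-6 band imply a maximum of 6. The literal rule gives items 1 and 2 one point each for *often* or *sometimes*, items 3, 5 and 6 one point each for *yes*, and item 4 nothing. The maximum is 1 + 1 + 1 + 0 + 1 + 1 = 5. Enumerating all allowed response patterns, 4 × 4 × 3 × 3 × (4 + 1 + 1) = 864, confirms it. The value 6 is not reproduced, and the 5-6 band is reached only by affirming all five other items.

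**Step 2: the two overlapping answers.** The possible month counts after a *yes* at item 3 are 1, 2 and 3.
- "some months, but not every month" fits 1 and 2.
- "only 1 or 2 months" fits 1 and 2.

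The sets are identical.

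**Step 3: effect of counting or not counting an item 4 answer.** Let item 3 be *yes* and let k of items 1, 2, 5 and 6 be affirmed. The score is 1 + k if the item 4 answer does not count and 2 + k if it does.

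| k | Patterns | Score, not counted | Score, counted | Band changes? |
|---|---|---|---|---|
| 0 | 1 | 1 | 2 | yes (0-1 to 2-4) |
| 1 | 4 | 2 | 3 | no |
| 2 | 6 | 3 | 4 | no |
| 3 | 4 | 4 | 5 | yes (2-4 to 5-6) |
| 4 | 1 | 5 | 6 | no |

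The score differs by 1 in all 16 patterns, and the band differs in 1 + 4 = 5 of them. If one overlapping answer is counted and the other is not, this is the gap between two truthful answers from the same household.

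**Step 4: the possible repairs disagree.** Treat *often* and *sometimes* as one affirmative and leave out declined items. There are then 16 × (1 + 3) = 64 complete patterns. Against the literal rule, the band changes in:
- 5 patterns if only the most frequent answer counts;
- 2 × 5 = 10 if the first two answers count;
- 3 × 5 = 15 if all three count.

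The maximum is 6 in each case. The protocol does not say which coding is meant.

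**Step 5: counting all three.** Item 4 then scores 1 for every *yes* at item 3, except where the parent declines item 4. Such a household scores at least 1 + 1 = 2 from that one experience and cannot fall in the 0-1 band.

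**Step 6: scale.** With 15 households, one household moved by 1 point shifts the mean by 1/15 = 0.07 points. One household moved across a band shifts that band's share by 1/15 = 6.7 percentage points.

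**The case against.** The strongest reply is that the literal reading is the least plausible one. Section 7.2.2 names a six-item scale, gives a 5-6 band and cites a source, so item 4 is clearly meant to score and the bracketed list may be shorthand. This stands as to intent. It does not supply the missing information: the qualifying item 4 answers are not listed, and whether the cited source settles them cannot be checked from the protocol. Even if it does, the two answers still coincide in the window this form uses.

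A second reply is that the overlap does no harm under some codings. That is correct. If item 4 never counts, if only the most frequent answer counts, or if all three count, ticking one overlapping answer rather than the other changes nothing. A reader might infer that parents will show false improvement from T1 to T4 in any event. The documents do not support that: it needs a coding that counts one of the two and not the other, such as reading *some months* as *sometimes*.

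A reader might also infer that declined answers are scored as food secure. The protocol states no rule for them, and a statistical analysis plan not shown here may set one.

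The lead-in to items 1 and 2 uses 6 months, which is a separate discrepancy. It does not affect this argument, because item 3 states its own 3-month window.

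**Conclusion.** The point holds in a limited form. As written, item 4 cannot contribute to the score, and two of its answers cannot be told apart. The literal range is 0-5 where 0-6 is implied. Counting one overlapping answer and not the other leaves a 1-point ambiguity for a household answering *yes* to item 3, with a band change in 5 of 16 patterns. That is a count of possible patterns, each given equal weight; the documents do not say how often each will occur.

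Two stronger readings go too far. The bands are not shown to be wrong: no cut-point is contradicted, and all three bands can be reached even under the literal rule. Nor is food insecurity the main exploratory signal: objective 2.3.1 and endpoint 3.3.1 list it with several other domains and rank none of them.

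The effect is confined to an exploratory, descriptive score and to the SD and CI that will help plan the efficacy trial. The primary feasibility endpoint (sections 3.1.1 and 8.3.1) does not use the score. The change is still worth making, because it is cheap now and the overlap cannot be resolved from collected data.

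**What to change.** Before the form is first used:

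1. In section 15.2.2.1, give item 4 mutually exclusive answers for the recall window used. For a 3-month window these could be all 3 months, 2 of 3 months, and 1 of 3 months.
2. In section 7.2.2, list which item 4 answers score 1.
3. In section 7.2.2, state that item 4 scores 0 when it is skipped because item 3 is *no*.

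The third sentence keeps in the change score those households that move between *yes* and *no* at item 3. Restricting change to households with the same items answered at T1 and T4 would drop them, so that restriction should not be adopted.

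The cost is one form item and two sentences of scoring rule. The downside is a small departure from the wording of the established item.
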